### Monitoring

The present trial will be supervised and monitored by a project manager (MK) and a research advisor (HM). They will examine the trial procedures to ensure data quality and compliance with the trial protocol. The findings of the trial monitoring will be reviewed by the Data Monitoring Committee (DMC).

## Discussion

A diet rich in antioxidants [11], polyphenols [12], and phytochemicals [13] has been shown to have a beneficial role in prediabetes. According to the beneficial properties of curcumin or zinc and inadequate evidence, RCTs are needed to assess the effect of curcumin and zinc co-supplementation on glycemic measurements, lipid profiles, and inflammatory and antioxidant biomarkers in prediabetic patients. The several strengths of this trial are the evaluation of (1) the effect of zinc and curcumin co-supplementation on native prediabetic patients for the first time; (2) the adherence to co-supplementation; (3) the side effects of co-supplementation; (4) healthy lifestyle education (PA and dietary intake) weekly; (5) dietary weight-loss interventions, individually; and (6) glycemic measurements (FPG, 2hpp, HbA1c, IR, IS, BCF, and insulin), lipid profiles (TG, TC, HDL-C, LDL-C, and VLDL), inflammatory (IL-1B and hs-CRP) and antioxidant (SOD, TAC, and MDA) biomarkers, liver enzyme (ALT and AST), serum zinc, urine zinc, anthropometric measurement (weight, height, WC, HC, BMI, WHtR, WHR, FM, FFM, MM, and ABSI), dietary intake, PA, HRQOL, DBP, and SBP, simultaneously.

This study will have several limitations. First, the prediabetes diagnosis duration will not be considered. A different duration may cause more bias in the results. Short prediabetes duration at baseline was associated with a higher probability of meeting optimal care goals such as remission of prediabetes and prevents type 2 diabetes. Second, the self-reported dietary intake in this study is subject to biases. Third, self-selection bias may occur; due to the recruitment of the participants is being achieved via voluntary participation by interested subjects. These participants may be potentially cautious and more health-conscious. However, the randomization will decrease this bias. Finally, the results of this trial are not generalizable to other populations (the participants with a BMI of normal or greater than 35 kg/m^2^, children, adolescents, and the elderly), due to only recruit prediabetes adults with a 25 ≤ BMI ≤ 35 kg/m^2^.

We hope the results of the present trial, negative or positive, (1) fill this gap in the literature (the diverse recommendations are proposed to improve prediabetes such as lifestyle modification (diet plus exercise), taking herbal medicine, or taking the pharmacological drug); however, the combination therapy may be more beneficial in preventing some complications and lowering side effects, and cost-effective [57], and (2) facilitate the approach for a much larger, multi-center clinical trial.

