### Demographic and medical information

The demographic and medical history data include gender, age, full address, postal code, marital status, income, occupation, ethnicity, educational background, smoking history, alcohol consumption, family history of diabetes or/and hypertension, medication history (dosage and type of drugs), and the diagnosis time of prediabetes.

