### Statistical analysis

Before statistical analysis, all data will be reviewed to check the accuracy and completeness. The primary analysis will be conducted on the intention-to-treat (ITT) population. Per-protocol (PP) and sensitivity analyses may be conducted as appropriate. The normality of data will be checked by the Kolmogorov-Smirnov test. The variables will be reported as mean ± SD or median (*Q*). The percentage changes for each variable will be separately reported and calculated by the following formula:
$$ \left[\left(E-B\right)/B\times 100\right], $$

where *E* and *B* are the end value and the baseline value of the variable, respectively.

According to the normality assumption, the significant changes between the groups will be assessed through a one-way analysis of variance (one-way ANOVA) with post hoc (LSD) analysis or Kruskal-Wallis. Changes from the baseline to post-intervention within the groups will be illustrated through a paired *t* test or Wilcoxon signed-rank test. The qualitative and quantitative variables in the two groups will be compared using the chi-square and *t* test, respectively. If necessary, the analysis of covariance (ANCOVA) will be used to control the potential confounding variables.

All analyses will be performed using a statistical software package (SPSS), version 22.0 (SPSS, Inc., Chicago, IL, USA), or NCSS2020. Statistical significance will be determined at *p* < 0.05.

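### Time since prediabetes diagnosis is recorded and named as a possible source of bias, but is said not to be considered, while the main test is unadjusted and ANCOVA is open-ended (minor)

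*Protocol article*

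**What the plan says.** Three sections of the protocol article bear on this.

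- **Demographic and medical information** lists among the items to be collected "medication history (dosage and type of drugs), and the diagnosis time of prediabetes".
- **Discussion (limitations)** states "the prediabetes diagnosis duration will not be considered. A different duration may cause more bias in the results", and gives the reason: "Short prediabetes duration at baseline was associated with a higher probability of meeting optimal care goals", with remission and prevention of type 2 diabetes as the examples.
- **Statistical analysis** compares changes between groups by "one-way analysis of variance (one-way ANOVA) with post hoc (LSD) analysis or Kruskal-Wallis". Covariates enter through one sentence: "If necessary, the analysis of covariance (ANCOVA) will be used to control the potential confounding variables". It names no covariate and does not say what would make adjustment necessary.

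Randomization and blinding describes blocks of four and states no stratification factor, so nothing stated there balances duration across arms.

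**The concern.** A limitation normally describes something the design cannot repair. Here the variable precedes randomisation, is to be recorded, and is said by the authors to relate to how patients fare. It can be put in a model or a baseline table without further data. Instead the article says that it will not be considered.

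Two things are at stake. With 21 participants per arm, a chance difference in a prognostic baseline factor can move an arm contrast, and the variation it would explain stays in the error term. In addition, because the ANCOVA sentence has neither a trigger nor a covariate list, duration could be left out or brought in after the data are seen. Either choice would be compatible with the text, across 18 biochemical parameters listed under the primary objective.

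**Working it through.** **The plan's own figure.** The Sample size section uses n = (S₁² + S₂²)(1.96 + 0.84)² / (difference)², with α = 0.05 two-sided and 80% power.

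- Curcumin: difference 3.64 − (−7.54) = 11.18, SDs 8.17 and 7. n = 7.27, rounded up to 8.
- Zinc: difference 16 − 3 = 13, SDs 12.8 and 15.3. n = 18.48, rounded up to 19.
- Allowance for loss: 19 × 1.10 = 20.9, rounded up to 21; 21 × 4 = 84.

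The stated 8, 19 and 84 reproduce. Nothing below changes them.

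**Inputs for the value of adjustment.** The SDs are root-mean-square values from the same section:

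- Zinc: √((12.8² + 15.3²)/2) = 14.1.
- Curcumin: √((8.17² + 7²)/2) = 7.6.

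The section prints no units. I take mg/dl, as in the eligibility criteria for FPG. The correlation r between duration and FPG change, after baseline adjustment, is given nowhere, so 0.1 to 0.3 is an assumption.

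**Formulas.**

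- Share of residual variance removed: r².
- Equivalent extra participants: 84 × (1/(1 − r²) − 1).
- Power: Φ(13 / (14.1 × √(1 − r²) × √(2/n)) − 1.96), with n = 19 completers per arm, or n = 38 per side when two arms are pooled on a factorial margin.
- Standard error of the difference in mean duration between two arms of 21, in SD units: √(2/21) = 0.31.
- Shift in the FPG contrast for a one-SE imbalance: r × 0.31 × SD.

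| Assumed r | Variance removed | Extra participants | Power, 19 v 19 | Power, 38 v 38 | Shift, SD 14.1 (mg/dl) | Shift, SD 7.6 (mg/dl) |
|---|---|---|---|---|---|---|
| 0 | 0% | 0 | 81.1% | 98.0% | 0 | 0 |
| 0.1 | 1% | 0.8 | 81.5% | 98.1% | 0.4 | 0.2 |
| 0.2 | 4% | 3.5 | 82.6% | 98.4% | 0.9 | 0.5 |
| 0.3 | 9% | 8.3 | 84.6% | 98.8% | 1.3 | 0.7 |

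The pairwise gain at r = 0.3 is 84.6 − 81.1 = 3.5 points. The largest shift is 1.3/13, one tenth of the difference planned for zinc; for curcumin it is 0.7/11.18, about 6%. These shifts are upper figures, because r is defined after baseline adjustment and the SDs are not; the adjusted SD can only be equal or smaller. On a 42 v 42 margin the standard error of imbalance falls to √(2/42) = 0.22 SD.

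**The case against.** The strongest reply is that a limitation is being treated as an analysis rule. The sentence is in the Discussion, and it does not say whether duration is ignored for eligibility, stratification or analysis. Eligibility and randomisation do ignore it, so the sentence is true on those readings and collecting the date contradicts nothing. The ANCOVA sentence excludes no variable. That stands. A reader might infer that the plan discards a free adjustment, but the article does not go that far.

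A reader might also infer that the trial will be biased, since the article uses that word. It will not be in any systematic sense: randomisation leaves only chance imbalance, and the unadjusted standard error already allows for it.

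Nor does the article show that duration predicts the trial's outcomes. Its statement concerns care goals such as remission, which are not outcomes here; no link to 90-day change in FPG, lipids or other markers is given. The recorded item dates diagnosis, not onset. Participants are screened at the first appointment, so anyone first detected there has a duration of about zero.

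Finally, covariate choice and coding are commonly left to an analysis plan, which is not shown. This stands for the coding details. It does not remove the need to reconcile the text: the article itself states how a named, collected variable will be treated, and beside it sets an unadjusted main test with an unspecified fallback.

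**Conclusion.** The point holds as a minor one. The data-collection, limitations and analysis sections do not fit together, and the open-ended ANCOVA is the weaker part of the plan behind it. Validity is not threatened.

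What is lost is modest: under the assumed r of 0.1 to 0.3, 1% to 9% of residual variance, less than 4 points of pairwise power, and at most about 0.7 to 1.3 mg/dl on the FPG contrast for a one-SE imbalance at the top of that range. These sizes rest entirely on the assumed correlation and on the article's sample-size SDs. If duration is unrelated to 90-day change, or nearly all participants are newly diagnosed, the gain is close to nil.

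A change is still worth making, because a prespecified model containing the baseline outcome value improves on an unadjusted test with ANCOVA left to later judgement, and the duration item is to be collected anyway.

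**What to change.** 1. In Statistical analysis, name ANCOVA with the baseline value of the outcome as the between-group model for the day-90 outcomes, in place of adjustment only where judged necessary.
2. Include time since diagnosis, with newly detected participants coded as zero, as a prespecified covariate in that model or in a named sensitivity analysis. State which.
3. Tabulate time since diagnosis by arm with the other baseline data.
4. Reword the limitation so that it agrees with the data-collection and analysis sections. If the authors mean only that duration is not used for eligibility or stratification, say so, and drop the suggestion of systematic bias.

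The cost is a few sentences, no new data, and one degree of freedom for duration. The downside is little return if most participants are first diagnosed at screening.

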### Trial status

The recruitment of this trial with ID number NRC-9810 on October 20, 2019, was begun in January 2020, and it seems the recruitment will be completed in December 2020 (now, it is performing).

## Data Availability

The datasets analyzed during the current study will be available from the corresponding author on reasonable request. Also, the results of this research will be published as the manuscripts in the valid databases and the Iranian Registry of Clinical Trials (IRCT) record will be updated.

## Abbreviations

ABSI: A Body Shape Index
ADA: American Diabetes Association
AEs: Adverse events
AGEs: Advanced glycation end-products
ANCOVA: Analysis of covariance
AST: Aspartate aminotransferase
ALT: Alanine aminotransferase
BCM: Beta cell function
BMC: Bisdemethoxycurcumin
BMD: Bone mineral density
BMI: Body mass index
BP: Blood pressure
CONSORT: Consolidated Standards for Reporting Trials
CUR: Curcumin
DBP: Diastolic blood pressure
DMC: Demethoxycurcumin
DLP: Dyslipidemia
FDA: Food and Drug Administration
FFM: Free fat mass
FM: Fat mass
FO: Fish oil
FPG: Fasting plasma glucose
F/M: Female/male
GRAS: Generally recognized as safe
HC: Hip circumference
HbA1c: Hemoglobin A1c
HDL-C: High-density lipoprotein cholesterol
HOMA: Homeostasis model of assessment
HRQOL: Health-related quality of life
hs-CRP: High-sensitivity C-reactive protein
IDF: International Diabetes Federation
IGT: Impaired glucose tolerance
IL-1B: Interleukin-B
IPAQ-SF: Short Form of International Physical Activity Questionnaire
IQR: Interquartile range
IRCT: Iranian Registry of Clinical Trials
IR: Insulin resistance
IS: Insulin sensitivity
LDL-C: Low-density lipoprotein cholesterol
MDA: Malondialdehyde
MET: Metabolic equivalent of task
MM: Muscle mass
MetS: Metabolic syndrome
NAFLD: Non-alcoholic fatty liver disease
One-way ANOVA: One-way analysis of variance
Pre-D: Prediabetes
pre-HTN: Prehypertension
QUICKI: Quantitative Insulin Sensitivity Check Index
RCT: Randomized clinical trial
SAE: Serious adverse events
SBP: Systolic blood pressure
SD: Standard deviation
SE: Standard error
SF-36: Short Form Health Survey
SPSS: Statistical Software Package
sUA: Serum uric acid
SUSAR: Suspected unexpected serious adverse reaction
TAC: Total blood antioxidant capacity
T/C: Treatment/control
TC: Total cholesterol
TG: Triglycerides
T2DM: Type 2 diabetes mellitus
VLDL: Very low-density lipoprotein
WC: Waist circumference
WHO: World Health Organization
WHR: Waist-hip ratio
WHtR: Waist-height ratio
2hpp: 2 h post-prandial
